#### 2.5.4. Data Collection and Questionnaire

Data will be collected using an online self-report questionnaire hosted on Google Forms ©, designed according to best practices in survey methodology [89]. Online surveys are particularly suitable for research on sensitive topics, as they promote honest responses, reduce social desirability bias, and enhance data reliability [107].

The questionnaire consists of seven sections with a total of 90 closed-ended items. The first section gathers sociodemographic information, the second collects professional or academic data (distinguishing between MHNs and NSs), and the third evaluates attitudes toward CMs and STs. The subsequent sections include three validated Italian instruments to measure psychological variables, and the final section assesses participants’ willingness to engage in the qualitative study.

Due to the lack of existing instruments to evaluate MHNs’ and NSs’ attitudes towards CMs and STs, the third section was developed by the authors. The method employed mirrors the approach used by Bowers and colleagues [108] in designing a survey to explore safety procedures and measures used in psychiatric units. The development process involved establishing the theoretical framework, performing a literature review, and conducting a focus group involving the authors and five experts: two mental health chief nurses, two nursing professors, and a statistician. To ensure clarity and relevance, content and face validity testing was conducted using established methodologies [109,110]. The content validity ratio (CVR) ranged from 0.60 to 1, exceeding the minimum threshold of 0.49 [111]. The item-level content validity index (I-CVI) ranged from 0.80 to 1, surpassing the cut-off of 0.70 [112]. Additionally, the scale-level content validity index (S-CVI/Ave) was 0.90, above the recommended threshold of 0.80 [109]. Evaluation of face validity further confirmed that the questions were clear, relevant, and applicable to the study’s objectives. Consequently, the items were deemed valid for administration.

The entire questionnaire was then tested on ten participants from each population to evaluate completion times, which ranged from 16 to 30 min. This length aligns with recommendations for maintaining participant engagement in online surveys [113]. The completion times are also consistent with the literature on web survey responses, where participants typically spend between one and ten seconds per question [114].

The questionnaire will be structured as follows:1.Sociodemographic variables: In this six-item section, participants will provide demographic information including sex, age, marital status, ethnicity, and spiritual beliefs. They will also indicate their current role (MHN or NS) to ensure they receive the appropriate subsequent questions. The anticipated completion time is two minutes.2a.Questions for MHNs: In this 14-item section, MHNs only will answer questions about their working role (i.e., clinical or chief nurse), educational level (e.g., bachelor’s or master’s degree), education in mental health nursing (i.e., yes or no), years of work experience, years of work experience in mental health, geographical region, work setting (i.e., acute, community, residential), contract type (i.e., permanent or fixed-term), work schedule (i.e., full-time or part-time), and work pattern (i.e., shift or daytime). They will also assess their perceived workplace safety, job satisfaction, intention to change work settings, and inclination to leave the profession, using a 5-point Likert scale (1 = not at all; 5 = very). The anticipated completion time is five minutes.2b.Questions for NSs: In this nine-item section, NSs only will be asked about the geographical region where their program is located, academic status (i.e., full-time or part-time student), year of enrolment, education in mental health nursing (i.e., yes or no), internship pattern (i.e., shift or daytime), and hours spent in mental health internships. Additionally, they will evaluate their academic satisfaction, intention to leave the program, and interest in working in the mental health field using a 5-point Likert scale (1 = not at all; 5 = very). The anticipated completion time is four minutes.3.Attitudes towards CMs and STs: In this eight-item section, participants will assess the appropriateness of CMs and STs commonly used in psychiatry according to the literature, including physical restraints, pharmacological restraints, locked ward doors, video surveillance systems, body-worn cameras, fixed alarms, portable alarms, and metal detectors. Responses will be collected using a 5-point Likert scale (1 = not at all appropriate; 5 = very appropriate). The anticipated completion time is four minutes.4.Depression Anxiety Stress Scale (DASS-21): This 21-item scale measures levels of depression, anxiety, and stress [115]. Participants will report the frequency of symptoms experienced over the past week on a 4-point Likert scale (0 = never; 3 = almost always). The total score for each dimension will be calculated. Internal consistency values are α = 0.82 for depression; α = 0.74 for anxiety; α = 0.85 for stress. The anticipated completion time is seven minutes.5.Opening Minds Stigma Scale for Healthcare Providers (OMS–HC): This 12-item scale measures stigma towards mental illnesses, focusing on attitudes towards people with mental illnesses and disclosure of mental illness [116]. Participants will indicate their agreement with each statement using a 5-point Likert scale (0 = strongly disagree; 4 = strongly agree). Higher scores indicate greater levels of stigma. Internal consistency values are α = 0.74 for stigma towards people with mental illness and α = 0.86 for stigma towards disclosure. The anticipated completion time is five minutes.6.Healthcare Professional Humanization Scale (HUMAS-I): This 19-item scale evaluates the humanization of care across five dimensions: affection, self-efficacy, emotional understanding, optimistic disposition, and sociability [117]. Participants will rate the frequency of their experiences using a 5-point Likert scale (1 = never; 5 = always). Aggregate scores will be calculated for each dimension and the overall scale. Internal consistency values are as follows: α = 0.87 for affection; α = 0.82 for self-efficacy; α = 0.81 for emotional understanding; α = 0.82 for optimistic disposition; α = 0.70 for sociability. The anticipated completion time is seven minutes.7.Willingness to participate in an interview: A dichotomous question (yes/no) will determine participants’ willingness to engage in the interview.

#### 2.5.5. Data Analysis

Descriptive and bivariate statistical methods will be used to analyze the data. Frequencies, percentages, medians, means (Ms), standard deviations (SDs), and quartiles will be calculated for all variables. To verify the assumptions required for parametric testing, normality will be assessed using the Shapiro–Wilk test, and homogeneity of variances will be evaluated with Levene’s test [118]. Correlations will be investigated through Pearson’s correlation for normally distributed continuous data, while Spearman’s rho will be used for non-normally distributed continuous data, ordinal data, or data with relevant outliers [119]. Differences in attitudes between groups will be assessed using independent samples t-tests for two-group comparisons and one-way ANOVA for comparisons involving more than two groups [120]. Significant findings from ANOVA will be further analyzed with Tukey post hoc tests to identify group differences. Potential confounding variables, such as sociodemographic and psychological factors, will be controlled through stratification, ensuring that these variables remain constant within subgroups [121]. Missing data will be excluded from the dataset to mitigate the risk of bias. All statistical analyses will be performed using SPSS© software (version 26), with a significance level set at *p* < 0.05.

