## 2. Materials and Methods

### 2.1. Research Hypothesis

Based on the literature and the conceptual framework developed, the following research hypotheses were formulated:(1)Attitudes toward coercive measures and security technologies in psychiatric settings differ between mental health nurses and nursing students.(2)In mental health nurses and nursing students, attitudes toward coercive measures and security technologies in psychiatric settings vary depending on the specific type of strategy considered.(3)In mental health nurses and nursing students, attitudes toward coercive measures and security technologies in psychiatric settings are influenced by sociodemographic and psychological variables, including levels of depression, anxiety, stress, stigma toward mental illness, and humanization of care.

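### Levene's test is run but changes nothing: attitude comparisons go to t-test, ANOVA and Tukey whatever the variances, although group sizes may be unequal

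*Protocol article*

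**What the plan says.** Protocol article, 2.5.5 Data Analysis, states two checks: "To verify the assumptions required for parametric testing, normality will be assessed" with the Shapiro–Wilk test, and Levene's test for homogeneity of variances. What follows differs by type of analysis.

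- Correlations: the choice depends on the data. Pearson is used for normal continuous data; Spearman's "rho will be used for non-normally distributed continuous data, ordinal data, or data with relevant outliers".
- Group differences in attitudes: independent samples t-tests for two groups and one-way ANOVA for more than two, with no condition attached. Then: "Significant findings from ANOVA will be further analyzed with Tukey post hoc tests to identify group differences".

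The outcome is defined in 2.5.4, questionnaire section 3: "In this eight-item section, participants will assess the appropriateness of CMs and STs commonly used in psychiatry according to the literature". On the format: "Responses will be collected using a 5-point Likert scale (1 = not at all appropriate; 5 = very appropriate"). No total or sub-score is defined for this section. For the DASS-21, by contrast, "The total score for each dimension will be calculated", and aggregates are also defined for the HUMAS-I. Hypothesis 2 in 2.1 expects attitudes to "vary depending on the specific type of strategy considered", which needs the items analysed separately.

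Section 2.5.3 sets a minimum of 384 for each population. It sets no maximum and no ratio between nurses and students.

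**The concern.** Levene's test has a purpose only if its result, or a method that makes it unnecessary, determines the comparison that is run. Here nothing written depends on it. Classical one-way ANOVA and Tukey assume equal variances, and so does the pooled version of the t-test. They tolerate unequal variances when group sizes are equal, but not when sizes differ as well.

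Unequal sizes are possible at three levels:

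- nurses versus students, because only a minimum is set;
- subgroup factors such as clinical or chief nurse, contract type, and acute, community or residential setting;
- strata, because 2.5.5 controls confounding by stratification.

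At stake are the p-values for hypothesis 1 and for the multi-group comparisons. They would be too small when the smaller group is the more variable, and too large when the larger group is.

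**Working it through.** **Inputs from the protocol article.** Eight items scored 1 to 5 (2.5.4); at least 384 per population (2.5.3); significance level 0.05, taken as two-sided because sidedness is not stated (2.5.5). The sample size reproduces: 1.96² × 0.5 × 0.5 / 0.05² = 384.16, stated as 384.

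**Assumed inputs.** The article gives no SDs, response distributions or expected subgroup sizes. All those below are assumptions, shown over a range.

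**Two groups, equal true means, pooled t-test (large-sample formula).**

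- Pooled variance: sp² = [(n1−1)s1² + (n2−1)s2²] / (n1+n2−2)
- SE used by the test: √[sp²(1/n1 + 1/n2)]
- True SE: √(s1²/n1 + s2²/n2)
- Type I error: 2 × [1 − Φ(1.96 × SE used / true SE)]

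Worked case, n = 384 and 1,000, SDs 1.3 and 0.9: sp² = (383 × 1.69 + 999 × 0.81)/1,382 = 1.0539. SE used = √(1.0539 × 0.003604) = 0.0616. True SE = √(1.69/384 + 0.81/1,000) = 0.0722. Then 1.96 × 0.0616/0.0722 ≈ 1.673, and the error is 9.4%.

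| n1 / n2 | SD1 / SD2 | SE used | True SE | Type I error |
|---|---|---|---|---|
| 384 / 384 | 1.3 / 0.9 | 0.0807 | 0.0807 | 5.0% |
| 384 / 500 | 1.3 / 0.9 | 0.0741 | 0.0776 | 6.1% |
| 384 / 1,000 | 1.1 / 1.0 | 0.0618 | 0.0644 | 6.0% |
| 384 / 1,000 | 1.2 / 1.0 | 0.0636 | 0.0689 | 7.1% |
| 384 / 1,000 | 1.3 / 0.9 | 0.0616 | 0.0722 | 9.4% |
| 384 / 1,000 | 0.9 / 1.3 | 0.0722 | 0.0616 | 2.2% |
| 84 / 300 | 1.3 / 0.9 | 0.1235 | 0.1511 | 10.9% |
| 84 / 300 | 0.9 / 1.3 | 0.1511 | 0.1236 | 1.7% |

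Simulated 5-point items at 84 versus 300 show how far this can go under larger variance differences. With the small group more variable, the pooled t-test rejected in 12.5% of runs (response variances 2.0 versus 0.8) and 24.0% (an extreme 3.36 versus 0.32). Welch stayed at 4.5–5.8% in these unequal-variance runs.

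**More than two groups.** In simulation with groups of 60, 120 and 200 and SDs 1.3, 0.9 and 0.9, classical one-way ANOVA rejects a true null in about 10% of runs (9% in a repeat run); Welch's ANOVA stays at about 5%. Tukey uses the same pooled error term: (59 × 1.69 + 119 × 0.81 + 199 × 0.81)/377 = 0.948. For 60 versus 200, the SE it uses is √[0.948 × (1/60 + 1/200)] = 0.143, against a true √(1.69/60 + 0.81/200) = 0.179, so it is about 20% too small. For 120 versus 200 it is 0.112 against 0.104, about 8% too large.

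**Non-normality alone.** Five assumed item shapes (symmetric, uniform, skewed, floor, bimodal) were simulated with identical distributions in both groups. At 384 versus 384, the pooled t-test's type I error was 4.4–5.3%. Shapiro–Wilk rejected normality in every sample for every shape, at n = 384 and at n = 30.

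**Would a rank test cure it?** With symmetric 5-point items, equal means, SDs 1.3 and 0.9, and 384 versus 1,000, Mann–Whitney rejects in about 9% of runs, the pooled t-test in 9–10% and Welch in 5–6%. The rank test shares most of the problem.

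**The case against.** Several objections have force.

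- **The nurse–student test may be sound.** Both populations have the same minimum, and the national totals (14,904 nurses, 55,842 students) do not predict who answers a convenience survey recruited through separate channels. At equal sizes the error is 5.0%. This stands: the distortion is conditional, and nothing shows that Levene's test will fail.
- **SPSS prints an unequal-variance row beside the t-test**, and the article does not specify the version. An analyst who runs Levene's test could well use that row. This stands as a possible reading for two groups, but the plan does not commit to it, and it names no counterpart for ANOVA or Tukey.
- **A journal article condenses.** A fallback could sit in a fuller document. But the article states the rule for group comparisons outright, without a condition, beside a conditional rule for correlations. The point concerns the rule as stated, not a missing detail.

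A reader might go further and infer that the t-test and ANOVA are invalid because the items are ordinal and will fail the normality check, so that rank tests must replace them. The figures above do not support that. Failing Shapiro–Wilk says little about a comparison of means at 384 per group, and Mann–Whitney does not remove the unequal-variance error. Nor does the article itself class the attitude items as ordinal. They plainly fit the class for which it reserves Spearman, but that is an inference, and it shows inconsistent handling rather than invalid tests.

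**Conclusion.** The point holds in a limited form. Section 2.5.5 tests for equal variances, attaches no consequence, and fixes ANOVA and Tukey, which depend on that assumption; the t-test version is left open. If sizes and variances both differ, the nominal 5% becomes roughly 6–9% or 2% for nurses versus students under the moderate assumptions shown. It becomes about 11% or 2% in an assumed 84 versus 300 subgroup comparison, and about 10% for the assumed three-group ANOVA. If sizes are equal, the two-group test keeps its level.

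All SDs and all unequal sizes are assumptions, so these figures show sensitivity and do not forecast the trial's error rate. Non-normality is not the problem at this sample size. Shapiro–Wilk carries no useful information for these items and should not select the test.

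**What to change.** In 2.5.5, state that group differences in the attitude items will be tested with Welch's t-test (two groups) and Welch's ANOVA with Games–Howell post hoc comparisons (more than two groups), by default and without gating on Shapiro–Wilk or Levene. A rank-based or ordinal analysis may be added as a sensitivity analysis. That would match the use of Spearman for ordinal data, but it does not replace Welch as the remedy for unequal variances.

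The cost is a change of wording and a negligible loss of power when variances are equal. Sample size and data collection are unaffected. One limit should be known: in very small, strongly skewed subgroups Welch is not exact either. In simulation at 20 versus 364 with identical distributions it rejected in 6.9% (skewed item) and 8.4% (floor item) of runs, against 4.3% for the pooled test in both. Results from strata of that size should be read with caution under either method.

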### 2.4. Study Population

In Italy, nursing education consists of a three-year university program leading to a bachelor’s degree in Nursing, designed to provide general nursing competencies [94]. This program can offer exposure to mental health knowledge through multidisciplinary courses and internships within National Health Service institutions [95]. However, research indicates that national nursing curricula show considerable variability and lack standardization [96,97], and Italian nurses often graduate with limited psychiatric nursing education [47]. Furthermore, while post-graduate courses in mental health nursing are available, they are not mandatory for employment in psychiatric settings [98]. Based on this context, the study population is defined as follows:Nursing students: Students enrolled in a general nursing program, regardless of year of study, theoretical training, or mental health internship experience.Mental health nurses: Nurses employed in mental health settings, regardless of specialized training in mental health nursing.

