#### 2.5.3. Sample Size

According to the Italian Ministry of Health, there are 14,904 MHNs employed in public and private mental health settings across Italy [100]. Additionally, data from the Italian Ministry of University and Research indicate that 55,842 NSs are enrolled in nursing programs nationwide [101,102,103]. Given the lack of prior studies assessing attitudes toward CMs and STs among Italian MHNs and NSs, the prevalence of positive or negative attitudes in these populations is unknown. As a result, the prevalence will be assumed at 50%, which, according to the World Health Organization guidelines [104] and established methodologies for sample size determination in survey research [105], leads to the maximum sample size required.

The required sample size for each population will be determined using Cochran’s formula as outlined by Barlett and colleagues [105]:$$n=\frac{t^{2}*[p*\left(1-p\right)]}{e^{2}}$$
where n = required sample size; t = t-value (1.96 for a 95% confidence interval in populations with more than 120 subjects); p = assumed proportion (0.5 for a prevalence of 50%); and e = acceptable margin of error. This formula has been used in other recent healthcare publications [106].

Using this approach, considering a 95% confidence interval, a 5% margin of error, and a 50% assumed prevalence for maximization, the sample size required is shown below:$$n=\frac{1.96^{2}*[0.5*\left(1-0.5\right)]}{0.05^{2}}\approx 384$$

Thus, to ensure the statistical significance of the results, the survey will include at least 384 participants from each population.

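### Stratification is the only confounder control named; it does not hold continuous factors constant and cannot adjust the psychological scores for one another, as hypothesis 3 needs

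*Protocol article*

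**What the plan says.** The analysis section (2.5.5) opens: "Descriptive and bivariate statistical methods will be used to analyze the data". It then names Pearson or Spearman correlations and, for group differences, the following: "Differences in attitudes between groups will be assessed using independent samples t-tests for two-group comparisons and one-way ANOVA for comparisons involving more than two groups". Tukey tests follow a significant ANOVA. The only sentence on confounding is: "Potential confounding variables, such as sociodemographic and psychological factors, will be controlled through stratification, ensuring that these variables remain constant within subgroups". No regression or other multivariable adjustment appears anywhere in the article.

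The hypotheses (2.1) ask whether nurses and students differ (hypothesis 1) and whether attitudes "are influenced by sociodemographic and psychological variables, including levels of depression, anxiety, stress, stigma toward mental illness, and humanization of care" (hypothesis 3). The second primary aim (2.2) concerns the associations between attitudes and these same variables.

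On sample size (2.5.3), "the survey will include at least 384 participants from each population", a figure obtained by "considering a 95% confidence interval, a 5% margin of error, and a 50% assumed prevalence for maximization". Students are eligible "regardless of year of study, theoretical training, or mental health internship experience" (2.4), while nurses with under one year in mental health are excluded (2.5.1).

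**The concern.** Three things do not fit together.

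- **The statement about stratification is wrong for much of what it covers.** Sociodemographic and psychological factors include age and the scale scores. These vary within any stratum wide enough to be useful. If age or years of experience are collected in bands, the band is constant but the underlying quantity is not.
- **Only a few factors can be crossed.** Whichever are chosen, the remainder are uncontrolled.
- **Hypothesis 3 needs mutual adjustment.** Depression, anxiety, stress, stigma and humanization are its exposures, and section 2.5.5 also lists psychological factors as confounders. That is not a contradiction, since each exposure may confound the others. Separating them, however, requires entering them together, which correlations and strata taken one factor at a time do not do.

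At stake is the second primary aim. A score could be reported as related to attitudes, after what is described as confounder control, when it only tracks another score or age.

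**Working it through.** **Inputs.** 384 per population (2.5.3); alpha 0.05 (2.5.5), taken as two-sided; factor lists (2.5.4). The confounder correlation r is assumed, over the range 0.2 to 0.5.

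**1. The plan's own figure.** 1.96² × 0.5 × 0.5 / 0.05² = 384.16, which reproduces 384. It fixes the precision of one proportion and says nothing about adjusted associations.

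**2. Number of candidate factors.**
- Nurses: 5 sociodemographic + 14 professional + 3 DASS-21 + 2 OMS-HC + 5 HUMAS-I = 29.
- Students: 5 + 9 + 3 + 2 + 5 = 24.
- Shared by both groups (hypothesis 1): 5 + 3 + 2 + 5 = 15, in at least 2 × 384 = 768 people.

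**3. How many can be crossed.** The mean cell size with k binary factors is 384/2^k: 48 for k = 3, 24 for k = 4, 12 for k = 5, 6 for k = 6. To keep at least 20 per cell, four binary factors is the limit. With 768 people it is five (768/32 = 24).

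**4. Variance left inside strata**, for a standard normal confounder cut at quantiles. This is 1 minus the mean squared stratum mean.
- Median split: 1 − 2/π = 0.363.
- Tertiles: outer stratum means ±1.091, middle 0, so 1 − (2/3) × 1.091² = 0.207.

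**5. Effect on the test.** Let exposure and outcome each correlate r with the confounder and be otherwise unrelated. With share v of the confounder's variance left within strata, the spurious within-stratum correlation is

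ρ = r²v / (r²v + 1 − r²).

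With z = atanh(ρ) × √380, the rejection rate is about Φ(z − 1.96) + Φ(−z − 1.96).

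- r = 0.5, median split: ρ = 0.0908/0.8408 = 0.108, z = 2.11, rate 56%.
- r = 0.2, median split: ρ = 0.0145/0.9745 = 0.0149, z = 0.29, rate 6%.

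| r | No adjustment (v = 1) | Median split (v = 0.363) | Tertiles (v = 0.207) | Continuous term (v = 0) |
|---|---|---|---|---|
| 0.2 | 12% | 6% | 5% | 5% |
| 0.3 | 42% | 10% | 7% | 5% |
| 0.4 | 88% | 24% | 11% | 5% |
| 0.5 | >99% | 56% | 24% | 5% |

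Simulation at n = 384 with a few thousand replicates agrees to about one percentage point: 7% to 55% for the median split, 6% to 24% for tertiles.

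**6. Can a model be fitted instead?** 384/29 ≈ 13 and 384/24 = 16 people per factor, and fewer per parameter once multi-category factors are coded. A main-effects model is possible, but a limited covariate set is preferable.

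**The case against.** There are several fair points on the other side.

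- **Joint stratification is not stated.** A reader might infer that all 24 to 29 factors are to be crossed in 384 people. The text does not say so, and crossing one to four coarse factors is feasible. Which factors and cut-points apply may sit in a fuller plan. This stands, so cell counts for a full cross-classification are not evidence against the plan. The choice of bivariate methods plus stratification, and the claim of constancy, are stated outright and are not details left elsewhere.
- **The inflation depends on an assumption.** At r = 0.2 to 0.3 with tertiles, a single confounder is handled almost at the nominal level. The 56% figure is the top of the range and should not be quoted alone. This stands too. Factors left out of the strata, however, fall in the unadjusted column.
- **Hypothesis 1 asks only whether the roles differ.** A crude contrast answers that. Age and experience are part of what separates a student from an employed nurse, so adjusting for them changes the question, and overlap in age may be poor. A reader might infer that the groups differ in age by design. Sections 2.4 and 2.5.1 contain no age criterion; only the asymmetry in mental health exposure is documented.
- **The second primary aim speaks of associations, not independent ones.** True, but the plan itself undertakes to control confounding by these variables, so its method should be able to do so.

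**Conclusion.** The point holds for hypothesis 3 and the second primary aim. Stratification as sole control does not keep age, experience or the scale scores constant, leaves most candidate confounders untouched at 384 per population, and gives no mutual adjustment of the psychological scores. The size of the harm ranges from negligible to severe. It rests on an assumed single, normally distributed confounder with equal correlations of 0.2 to 0.5 with exposure and attitude, and on attitude items treated as continuous. The documents do not support saying that stratification can never work, or that the nurse–student comparison is invalid. For hypothesis 1 the gap is only that a crude difference cannot be attributed to role itself.

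**What to change.** In section 2.5.5:

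- **Hypothesis 3 and the second primary aim:** prespecify one multivariable regression per attitude item (ordinal logistic, or linear with robust standard errors), fitted separately for nurses and students. Name a limited set of sociodemographic and professional or academic covariates. Enter the DASS-21, OMS-HC and HUMAS-I scores together and as continuous terms, using the HUMAS-I total or its dimensions but not both.
- **Stratification:** keep it as a descriptive supplement and delete the claim that it holds the factors constant.
- **Hypothesis 1:** keep the crude nurse–student contrast as the answer to whether the roles differ. As sensitivity analyses, add a model adjusted for sex and age, and a comparison with students split by mental health education or internship hours. State that age overlap may be limited and that the adjusted result may then rest on extrapolation.
- **Wording:** express hypothesis 3 and its conclusions as association, since the survey is cross-sectional.

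Cost: a rewrite of one section and some wording, plus the fitting and checking of models for eight items in two populations. All the variables are already in the questionnaire, so no new data are needed.

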## Abstract

Background/Objectives: The use of coercive measures (CMs) and security technologies (STs) in mental healthcare continues to raise ethical and practical concerns, affecting both patient and staff well-being. Mental health nurses (MHNs) and nursing students (NSs) play a key role in the decision-making process regarding these interventions. However, their attitudes, particularly toward STs, remain underexplored in Italy. This study protocol aims to introduce a new conceptual framework and investigate Italian MHNs’ and NSs’ attitudes toward CMs and STs in mental health settings. Additionally, it will explore the influence of sociodemographic and psychological factors, including stress, anxiety, depression, stigma, and humanization on these attitudes. Methods: The research will be conducted in two phases. Phase 1 involves a national survey of a convenience sample of MHNs and NSs to assess their attitudes and related factors. Phase 2 includes qualitative interviews with a purposive sample of MHNs and NSs to explore participants’ perspectives on STs in more depth. Quantitative data will be analyzed using descriptive and inferential statistics, while qualitative data will be examined through thematic analysis. Conclusions: This study protocol seeks to enhance our understanding of MHNs’ and NSs’ attitudes toward the use of CMs and STs in mental health settings, identifying key factors influencing these attitudes. The findings aim to inform policy development, education programs, and clinical practices in both the Italian and international panoramas. Additionally, the proposed conceptual framework could guide future research in this field.

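### Every bivariate test is judged at p < 0.05, with no stated adjustment beyond Tukey within an ANOVA and no primary item or test family, so some of the reported key factors are likely to be chance findings

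*Protocol article*

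**What the plan says.** Section 2.5.5 (Data Analysis) opens with "Descriptive and bivariate statistical methods will be used to analyze the data" and closes by stating that every analysis is run in SPSS, "with a significance level set at *p* < 0.05". Between these it lists Pearson or Spearman correlations, two-sample t-tests and one-way ANOVA. On multiplicity it says one thing: "Significant findings from ANOVA will be further analyzed with Tukey post hoc tests to identify group differences". Stratification is named as the means of handling confounders, without saying how many strata or which variables.

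The outcome comes from section 3 of the questionnaire (2.5.4): "In this eight-item section, participants will assess the appropriateness of CMs and STs commonly used in psychiatry", "including physical restraints, pharmacological restraints, locked ward doors, video surveillance systems, body-worn cameras, fixed alarms, portable alarms, and metal detectors". No total or subscale score is defined for these items. Hypothesis 2 in section 2.1 expects that attitudes "vary depending on the specific type of strategy considered", which points to analysis item by item.

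Section 2.2 makes the associations with sociodemographic and psychological variables a primary aim, and section 2.1 states them as hypothesis 3. The Abstract describes the intended result as "identifying key factors influencing these attitudes", for use in policy, education and clinical practice.

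**The concern.** Eight outcomes are crossed with a long list of factors in two populations, and each resulting test faces the same unadjusted 5% threshold. Tukey protects only the pairwise contrasts inside one ANOVA. It does nothing across items, factors or populations.

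The product of the survey is a list of factors said to influence attitudes. If the list is built from whichever tests fall below 0.05, it will include some that do so by chance, and the plan has no rule for marking them. The eight items are answered by the same people, so chance results may also cluster on one factor and look like a consistent pattern.

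**Working it through.** **The plan's own figures.** Cochran's formula in 2.5.3 gives 1.96² × 0.5 × 0.5 / 0.05² = 384.16, which reproduces the stated 384 per population. The questionnaire sections add up as 6 + 14 + 9 + 8 + 21 + 12 + 19 + 1 = 90 items, as stated in 2.5.4, so the item counts used below are read correctly. The article gives no number of tests and no familywise error rate to reproduce.

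**Inputs, all from 2.5.4.**
- Outcomes: 8 attitude items.
- Sociodemographic factors: 5 (the sixth item in that section is role).
- Professional items, nurses only: 14. Academic items, students only: 9.
- Scale scores: 3 for DASS-21, 2 for OMS-HC, and 6 for HUMAS-I (five dimensions and the overall score), in total 11.

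**Full grid.** Nurses: 8 × (5 + 14 + 11) = 240. Students: 8 × (5 + 9 + 11) = 200. Nurse versus student: 8. Total 240 + 200 + 8 = 448. Expected chance results if every null is true: 448 × 0.05 = 22.4.

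**Other readings.** The article does not fix the grid, so the range matters:

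| Reading | Tests | Expected by chance, all nulls true |
|---|---|---|
| Full grid plus an OMS-HC total | 8 × (31 + 26) + 8 = 464 | 23.2 |
| Full grid | 448 | 22.4 |
| Full grid without the HUMAS-I overall score | 8 × (29 + 24) + 8 = 432 | 21.6 |
| Only total scores for OMS-HC and HUMAS-I | 8 × (24 + 19) + 8 = 352 | 17.6 |
| Shared factors tested once in the pooled sample | 8 × (5 + 11 + 14 + 9 + 1) = 320 | 16.0 |
| Sociodemographic and scale scores only, by population, plus role | 8 × 16 × 2 + 8 = 264 | 13.2 |
| The same factors, pooled | 8 × 17 = 136 | 6.8 |
| Two composite outcomes (not defined in the article) | 2 × (30 + 25 + 1) = 112 | 5.6 |

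The expected counts do not need independence. With independent tests, the chance of at least one false positive is 1 − 0.95¹¹² = 0.997 for the smallest reading and higher for the others.

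**If some nulls are false.** The expected number of false positives falls in proportion. If half of the 448 nulls are true, it is 448 × 0.5 × 0.05 = 11.2.

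**Tests versus factors.** The full grid has 30 + 25 + 1 = 56 factor-by-population units, each tested on eight items. With independent items and all nulls true, 56 × (1 − 0.95⁸) = 56 × 0.337 ≈ 18.8 units would show at least one significant item. Positive correlation between items would lower this number.

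**Hypothesis 1.** Eight nurse-student comparisons: 1 − 0.95⁸ = 0.337 if independent.

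**Not counted in the table.** Pairwise comparisons between strategies under hypothesis 2 would add up to 2 × (8 × 7 / 2) = 56. Stratified analyses would add an unstated number.

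**Cost of correction.** The detectable correlation at 80% power is r = tanh[(z for two-sided α + 0.84) / √(n − 3)], with n = 384. At α = 0.05: tanh[(1.96 + 0.84) / √381] ≈ 0.14. At α = 0.05/240: tanh[(3.71 + 0.84) / √381] ≈ 0.23.

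**The case against.** The case against has weight on several points.

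- **The count is a reconstruction.** The plan states no item-by-factor grid. Hypothesis 3 and the second primary aim speak of sociodemographic and psychological variables, while the professional and academic items form a separate questionnaire section and may only describe the sample. Those items supply (14 + 9) × 8 = 184 of the 448 tests. This stands, which is why a range is given.
- **A complete null is not the study's premise.** Section 1.4 cites published associations of coercion with sex, age, experience, anxiety, stress and stigma. This also stands. The upper figures are what chance would produce if nothing were associated, not a forecast.
- **The survey is descriptive in design.** It uses a convenience sample, its size rests on a 5% margin of error, and the topic is little studied. Strict error control in such work is partly a matter of choice. But the article labels nothing exploratory: it states hypotheses, makes the associations a primary aim and promises key factors for policy.
- **A fuller document may add an adjustment.** That is possible, and a 0.05 level could be applied to adjusted p-values. Still, 2.5.5 sets one level for all analyses and names one local procedure. The point rests on that text, not only on silence.

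A reader might infer that about 22 spurious factors will be reported. The documents do not support this: 22.4 counts tests, belongs to one broad reading and requires every null to be true. A reader might also infer that there is no multiplicity control at all, but Tukey is specified within each ANOVA. Nor are chance results wholly indistinguishable from real ones: correlation coefficients, means and standard deviations are planned, so readers can weigh the size and consistency of effects.

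**Conclusion.** The concern holds in this form: section 2.5.5 applies an unadjusted 5% level to a large and unstated number of bivariate tests, with no correction beyond Tukey and no primary item, composite or family. On the plausible readings there are about 110 to 460 tests. That implies about 6 to 23 item-by-factor results significant by chance if all nulls were true, and proportionately fewer otherwise. For hypothesis 1 alone, the chance of at least one false positive is about 34% if the eight comparisons are independent. These figures rest on the questionnaire as described in 2.5.4 and on item-level testing, which hypothesis 2 and the lack of any composite score suggest but do not prove. The defect remains under the narrowest reading. It does not invalidate the survey, and it is cheap to improve.

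**What to change.** Add a paragraph to 2.5.5 that defines the families and the correction for each:

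- Hypothesis 1: Holm at 5% across the eight nurse-student item comparisons.
- Hypothesis 2: Holm across any pairwise comparisons between strategies. Which test suits ratings of several strategies by the same person is a separate question.
- Hypothesis 3: Benjamini-Hochberg at a 5% false discovery rate, within each population, across all item-by-factor tests. List the factors so that the number of tests is fixed before the data are seen.
- Throughout: effect sizes with 95% confidence intervals, and an exploratory label for any result significant only before correction.

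No new data are needed, only a few more lines of analysis. The downside is some loss of power for small associations. In the worst case, Bonferroni over 240 tests with n = 384 and 80% power, the detectable correlation rises from about 0.14 to 0.23. Benjamini-Hochberg costs less than that.
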